#### Anxiety

We will measure anxiety using the anxiety items subscale from the PROMIS-29 + 2 Profile v2.1 (PROPr) [34] at baseline and week 4.

#### Sleep disturbance

We will measure sleep using the sleep disturbance items subscale from the PROMIS-29 + 2 Profile v2.1 (PROPr) [34] at baseline and week 4.

#### Suicide ideation

We will measure suicide ideation and vulnerability to suicide-related behavior with the PANSI [35] at baseline and week 4.

### Other measures

#### Demographics

We will use standardized case report forms to collect sex at birth, age, and race/ethnicity.

#### Daily assessments

We will ask participants to complete brief (< 5 min), daily questions for pain intensity, pain interference, and sleep quality using a 0–10 numeric rating scale, and record their daily cannabis use (i.e., product name, administration route, cannabinoid content, dose, timing, and side effects).

#### Fitbit data

Synced data from Fitbits will provide information that includes physical activity minutes, step count, sedentary time, sleep duration, and resting heart rate. We will ask participants to wear the Fitbits daily throughout the duration of the study for passive data collection.

#### Pain phenotypes

We will use the 2016 Fibromyalgia Survey Criteria to generate a continuous measure of nociplastic pain that ranges from 0 to 31 based on a self-report body map that assesses the number of painful sites as well as symptom severity for fatigue, cognitive problems, headache, and mood [7, 39, 40]. We will also measure neuropathic pain quality using painDETECT [41]. These combined measures will allow us to classify participants as having degrees of nociplastic pain and neuropathic pain, which may affect treatment response. We will collect these measures at baseline and week 4.

#### Social determinants of health

The screening survey will collect information about social determinants of health including employment status, household income, household size, financial strain, healthcare financial strain, transportation access, food insecurity, housing insecurity, social support, exposure to discrimination, and neighborhood cohesion and disorder [42–47].

### Safety and adverse events

We will ask participants to report adverse events on Day 1 (baseline), Day 7, Day 28 (week 4, end of treatment and primary outcome assessed), and Day 58 (end of follow up) via a brief questionnaire. Participants may also report adverse events as needed per institutional and FDA guidelines. If a participant reports pregnancy, we will withdraw them from the study. We will also ask participants about any new medications or supplements that they may have started taking, and whether they were diagnosed with a new medical condition. If this information suggests potential interactions with CBD, we will send participants for a blood draw in their local area to test liver function. Study investigators and physicians will determine whether a participant needs to be withdrawn from the study due to safety concerns on a case-by-case basis. Safety will also be a secondary outcome in this study.

### Data analysis plan

Primary analysis will use an intent-to-treat analysis and include all randomized participants regardless of their completion of the protocol. We will examine the distribution of variables and apply transformations if necessary. We will generate descriptive statistics such as means, medians, standard deviations, range, frequencies, and percentages overall and by intervention assignment, conditional on the scale of measurement.

The primary analysis will fit a linear regression model with the outcome of PGIC and main effect-coded binary predictor of CBD vs. placebo controlling for the stratification variable of sex at birth. We will use an alpha level of 0.05 for the main treatment effect of interest. We will include covariates such as age, race/ethnicity, baseline symptoms (e.g., anxiety, sleep disturbance), recruitment method (clinic vs. community engaged approach vs. social media/internet), concomitant medications, and pain phenotype (i.e., per the painDETECT and 2016 FM survey criteria) in secondary analyses. We will explore treatment effect modification by gender, CBD dose, and the above covariates by exploring treatment by covariate interactions using shrinkage methods. We will explore baseline sleep, anxiety, pain severity, and pain intensity, as possible mediators of the treatment effect with the primary outcome.

We will analyze secondary outcomes similarly using linear or generalized linear (depending on the outcome type) regression controlling for baseline value if recorded. To explore longitudinal changes, we will analyze weekly and daily outcomes using linear mixed effects models (with any transformation necessary). We will use mixed effects models with a random intercept for the participant and random slope of time and fixed effects of treatment arm, time, and the interactions between time and treatment to compare the treatment groups over time. In stratified analysis by treatment (CBD vs. placebo), we will assess the relationship between the primary and secondary outcomes and the average daily dose taken, and cumulative dose taken, separately.

Lastly, our exploratory analyses will consider daily assessments of pain-related symptoms, Fitbit data, and social determinants of health, e.g., whether activity levels or social risk factors moderate treatment efficacy.

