**Methods:**

We designed a randomized, double-blind, placebo-controlled, pragmatic clinical trial with 468 participants. Participants will be randomly assigned in a 1:1 ratio to receive either placebo or a CBD oral solution over a 4-week period. The trial is remote via a smartphone app and by shipping study materials, including study medication, to participants. We will compare the difference in PGIC between the CBD and placebo group after four weeks and impacts on secondary outcomes (e.g., pain severity, pain interference, anxiety, suicide ideation, and sleep disturbance).

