### Recruitment and retention

Our target sample size is 468 participants, which we selected to ensure sufficient power (i.e., at least 80%) to detect a relatively small Cohen’s d effect size (i.e., 0.30) for our primary outcome, PGIC, when assuming 25% attrition. We aim to recruit a study sample that is representative of the gender and racial/ethnic distribution of Veterans residing within the State of Michigan [36]. There are multiple resources available to us that will support recruitment for the proposed study. Based on medical chart review, we have identified 482 adult Veterans with chronic pain who have sought care through the University of Michigan Health System, and we will contact them with IRB approval. We will also recruit outside of the health system by contacting Veterans’ groups and organizations, attending Veteran-specific resource fairs, and sharing information at free community education events concerning chronic pain and the evidence-base for cannabis. We will supplement these recruitment approaches using the research volunteer registry, UMHealthResearch.com; targeted radio and social media ad campaigns; and word-of-mouth.

This study does not require in-person visits, which will support participant retention. We will compensate participants up to $60 for completing study-related surveys over 4 weeks. Additionally, participants will be able to keep the study Fitbit for personal use at the conclusion of the intervention.

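### The primary PGIC model adjusts only for sex at birth; fixing a short list of baseline covariates in advance could add precision at almost no cost

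*Protocol article*

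**What the plan says.** All of this is in the protocol article.

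- **Primary model** (Data analysis plan): the analysis is to "fit a linear regression model with the outcome of PGIC and main effect-coded binary predictor of CBD vs. placebo controlling for the stratification variable", namely sex at birth. No other covariate is in that model.
- **Secondary analyses** (same section): "We will include covariates such as age, race/ethnicity, baseline symptoms (e.g., anxiety, sleep disturbance", followed by recruitment method, concomitant medications and pain phenotype. Anxiety and sleep disturbance are the only baseline symptoms given as examples.
- **Mediators** (same section): baseline sleep, anxiety, pain severity and pain intensity are to be explored as possible mediators of the effect on PGIC.
- **Secondary outcomes** (same section): these are adjusted for their own baseline value where one was recorded.
- **Data collected:** the screening 0–10 pain rating and the PROMIS pain interference total are needed for eligibility (Inclusion criteria, Table 2). Pain interference, anxiety and sleep disturbance have baseline values (Secondary outcome measures), as do the 2016 fibromyalgia survey score and painDETECT (Pain phenotypes).
- **Sample size** (Recruitment and retention): "Our target sample size is 468 participants", for at least 80% power at an "effect size (i.e., 0.30) for our primary outcome, PGIC, when assuming 25% attrition".

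**The concern.** In a randomised trial with a linear model, adjusting for baseline covariates chosen in advance leaves the target of estimation unchanged. It removes outcome variance that those covariates explain and corrects for chance imbalance in them. For most continuous outcomes the baseline value of the outcome does this work. PGIC has none, so other pre-treatment scores would have to do it, and the primary model uses none of them. Randomisation is stratified by sex alone, so the design does not balance pain or phenotype either.

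The plan is also uneven. Secondary outcomes get baseline adjustment where possible, and the one confirmatory outcome does not. Baseline pain severity and intensity are expected to bear on PGIC but are given the role of mediator. A value recorded before treatment cannot be changed by treatment and so cannot carry its effect. Its natural role is as a covariate or an effect modifier.

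At stake is precision. At the planned attrition, power is close to the 80% floor, so a modest gain would be useful.

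**Working it through.** **Inputs.** From the article: 468 randomised, 1:1 allocation, d = 0.30, 25% attrition, power of at least 80%, alpha 0.05. Assumed: a two-sided test (sidedness is not stated, but two-sided reproduces the sample size), and R², the share of within-arm PGIC variance explained by the added covariates.

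**Step 1: reproduce the sample size.**
n per arm = 2(1.960 + 0.842)² / 0.30² = 174.4, rounded up to 175, so 350 in total.
Allowing for attrition: 350 / 0.75 = 467 in total; or 175 / 0.75 = 234 per arm, which is 468. The stated figure is reproduced. The t-test version needs 176 per arm and 352 / 0.75 = 470 in total, or 2 more than planned.

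**Step 2: power of the planned model.**
Evaluable: 468 × 0.75 = 351.
Normal approximation: Φ(0.30 / √(4/351) − 1.960) = Φ(2.810 − 1.960) = 80.2%. The t-test gives 80.0%. With no attrition (468 evaluable) the t-test gives 89.9%.

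**Step 3: add covariates.** The residual SD becomes √(1 − R²), so the standardised effect is 0.30 / √(1 − R²). The equivalent number of extra evaluable participants is 351 / (1 − R²) − 351.

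| Assumed R² | Power, t-test | Power, normal | Equivalent extra participants |
|---|---|---|---|
| 0 | 80.0% | 80.2% | 0 |
| 0.01 | 80.4% | 80.6% | 4 |
| 0.02 | 80.8% | 81.0% | 7 |
| 0.05 | 82.0% | 82.2% | 18 |
| 0.10 | 84.0% | 84.2% | 39 |
| 0.15 | 86.0% | 86.2% | 62 |

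**Step 4: cost if the covariates are useless.** With six covariates and R² = 0, the residual degrees of freedom are 351 − 2 − 6 = 343 and power is 80.02%, against 80.03% for the plain t-test.

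**The case against.** The strongest reply is that nothing here is wrong. The plan names its model in advance and includes the only stratification factor. The estimate is unbiased, and the sample size was set without counting on any covariate gain. All of that stands.

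It is also fair that the size of the gain is unknown. No figure in the article links a baseline score to PGIC. PGIC is already a rating of change, and eligibility cuts off the lower range of pain (at least 4) and interference (at least 11). R² could be small and the gain under 1 point.

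Four stronger readings are tempting, and the article does not support them:

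- **That the trial has no reserve.** Power sits at 80.0% only if the full 25% is lost and only observed outcomes count. It is about 90% with no attrition, and the plan includes all randomised participants with multiple imputation.
- **That baseline pain is assigned to the secondary covariate list.** The list does not name it; pain appears only in the sentence on mediators.
- **That a pre-dose mean of daily worst pain is available.** The Pain intensity section compares week 1 with week 4 of the intervention. The Eligibility criteria section mentions registry daily surveys but does not give their content. Week 1 pain would be a post-randomisation value.
- **That concomitant medications would bring post-randomisation data into the main result.** The article does not say that on-trial medicines are counted, the item concerns secondary analyses only, and an analysis plan that is not shown may settle it.

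The objection does not remove the point that the primary model is stated explicitly, that usable baseline scores are collected, and that adjusting for them costs almost nothing.

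**Conclusion.** The point holds as an optional efficiency improvement. The sex-only model is valid and meets the stated power, so there is no error to correct in the primary analysis or the sample size. Adjusting for a few baseline scores would raise power by less than 1 point at R² of 0.02 or below, and by about 2, 4 and 6 points at 0.05, 0.10 and 0.15. There is no material loss at R² = 0. These figures rest on a two-sided alpha of 0.05, 351 evaluable participants, d = 0.30 and the assumed R² values.

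Separately, the wording that treats baseline values as mediators cannot be right as it stands, whatever is decided about the primary model.

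**What to change.** Before unblinding, state the primary model as PGIC on arm, sex at birth and a short fixed list of covariates recorded before randomisation. For example: baseline PROMIS pain interference, the screening 0–10 pain rating, the 2016 fibromyalgia survey score, anxiety, sleep disturbance and age. Keep the sex-only model as a sensitivity analysis. Leave out daily worst pain unless a pre-dose value is confirmed to exist.

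Reword the mediator sentence so that baseline scores are covariates or effect modifiers.

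The cost is a sentence or two. No new data are needed for the listed covariates, provided that each is confirmed to have been recorded before randomisation, and the loss of degrees of freedom is negligible.

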Thus, we developed a protocol to investigate whether CBD improves overall pain symptoms and quality of life among Veterans with chronic pain via a pragmatic, randomized, double-blinded, and placebo-controlled trial using CBD oral solution. Our objective is to examine whether CBD oral solution compared with placebo study medication is associated with changes in pain and related symptoms over 4 weeks of use. Our primary outcome is the Patient Global Impression of Change (PGIC), which is often used in trials for chronic pain [21], while our secondary outcomes include pain severity, pain interference, sleep, suicide ideation, and mood. As part of this study, we will also phenotype pain and investigate whether pain related symptoms (i.e., secondary outcomes) contribute to global improvement. Consistent with other clinical trials of CBD, we expect adverse events to be rare and minor [22].

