#### Pain intensity

We will ask participants to report their “worst pain” level on a 0–10 numerical rating scale via a brief daily questionnaire. To assess change in pain intensity over the 4 weeks of the intervention, we will compare the average of pain intensity for week 1 relative to the average of pain intensity for week 4.

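### Baseline symptoms are planned as mediators of the PGIC effect, but a value fixed before the first dose cannot carry a treatment effect, so the stated aim on symptoms is not served

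*Protocol article*

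**What the plan says.** - **Planned analysis** (Data analysis plan): "We will explore baseline sleep, anxiety, pain severity, and pain intensity, as possible mediators of the treatment effect with the primary outcome".
- **Aim** (end of Background): the trial will "investigate whether pain related symptoms (i.e., secondary outcomes) contribute to global improvement".
- **Allocation** (Abstract, Methods): "Participants will be randomly assigned in a 1:1 ratio to receive either placebo or a CBD oral solution over a 4-week period". Under Trial procedures, the study medication is shipped only after randomisation.
- **Timing of the anxiety score**: "We will measure anxiety using the anxiety items subscale from the PROMIS-29 + 2 Profile v2.1 (PROPr) [34] at baseline and week 4".
- **Timing of the sleep score**: the same two time points, with the sleep items of the same instrument.
- **Pain intensity**, rated daily: "we will compare the average of pain intensity for week 1 relative to the average of pain intensity for week 4". Both weeks fall within the treatment period.
- **Meaning of baseline** (Safety and adverse events): "We will ask participants to report adverse events on Day 1 (baseline), Day 7, Day 28".
- **Other uses of baseline symptoms** (Data analysis plan): the covariates for secondary analyses include "baseline symptoms (e.g., anxiety, sleep disturbance", and the same covariates are then examined for interaction with treatment.

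Nothing in the article redefines the mediators as week 4 values or as changes.

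**The concern.** Mediation asks whether treatment moves an intermediate variable and whether that movement accounts for part of the effect on the outcome. A score taken before dosing is not intermediate. It may predict PGIC, or identify who benefits more, but those are the roles of a covariate and a moderator.

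The aim in the Background concerns the secondary outcomes, which are symptoms as they change on treatment. The mediation sentence is the only one in the Data analysis plan that links those symptoms to the treatment effect on PGIC. The mixed models compare arms over time, the within-arm analyses relate outcomes to dose, and the closing exploratory paragraph mentions daily symptoms but gives only moderation as its example. Carried out literally, the mediation analysis would suggest that sleep and anxiety do not explain any benefit even if they do. Occasionally it would present a chance imbalance as a mechanism.

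**Working it through.** **1. Sample size.** Inputs from Recruitment and retention: d = 0.30, power at least 80%, 25% attrition. Alpha 0.05 comes from the Data analysis plan; two-sided is assumed.
- n per arm = 2 × (1.960 + 0.842)² / 0.30² = 174.4, rounded up to 175.
- 175 / 0.75 = 233.3, rounded up to 234 per arm, so 2 × 234 = 468. The plan's figure is reproduced.
- Evaluable after attrition: 468 × 0.75 = 351, which gives 80.2% power (80.0% with the t distribution).

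**2. Expected indirect effect.** In the usual linear model, indirect effect = a × b. Here a is the arm difference in the mediator and b is the slope of PGIC on the mediator given arm. For a value fixed before the first blinded dose, randomisation makes a = 0 in expectation, so a × b = 0 whatever b is.

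**3. Size of chance imbalance.** For a variable with SD 1 and equal arms, SE of the difference = √(2/N + 2/N) = 2/√N.
- N = 468 (all randomised, e.g. with imputed PGIC): 2/√468 = 0.092 SD; 1.96 × 0.092 = 0.18 SD.
- N = 351 (evaluable): 2/√351 = 0.107 SD; 1.96 × 0.107 = 0.21 SD.

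**4. Simulation.** 20,000 trials of 351 participants, total effect 0.30 SD. Mediation was declared when both paths were significant at 0.05. The article gives no slopes, so the values of b are assumptions.

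| Baseline mediator, slope b | Mean indirect effect | SD across trials | Mediation declared |
|---|---|---|---|
| 0.2 | −0.0001 | 0.022 | 4.6% |
| 0.4 | −0.0002 | 0.043 | 5.1% |
| 0.6 | 0.0000 | 0.064 | 5.1% |

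The SDs agree with b × 0.107 (0.021, 0.043, 0.064). At b = 0.4 the chance range is 1.96 × 0.043 = ±0.084, or 0.084 / 0.30 = 28% of the assumed total effect in either direction. The treatment effect itself stays at about 0.30 with or without adjustment for the baseline variable.

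**5. Contrast.** With a post-randomisation mediator that treatment shifts by an assumed 0.30 SD, and b = 0.4, the mean indirect effect is 0.120, the direct effect falls to 0.180, and mediation is declared in about 80% of runs. This illustration assumes no confounding between mediator and PGIC.

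**The case against.** - **The analysis is exploratory.** This stands. The primary PGIC regression, its alpha and the sample size do not depend on it, and false mediation arises only at about the nominal 5% rate. A reader might infer that the trial's main conclusion is at risk; the article gives no support for that.
- **Zero is not certain for every variable.** This stands for pain intensity. Its outcome definition uses the week 1 average as the starting value. If that is the baseline meant, it is an on-treatment value and its path from treatment need not be zero. The article does not say so. A reader might infer that all four mediators must return exactly zero; that is secure only for values taken before dosing.
- **The sentence may be loose drafting.** Possibly. Baseline might qualify only sleep, and pain severity is listed beside pain intensity although the outcome sections define only intensity and interference. But on the narrow reading baseline sleep is still invalid and the other variables have no stated time point. If mediators is a slip for moderators, the Background aim has no evident analysis. The text needs correcting on each reading.
- **The baseline scores are already moderators.** This is only partly so. Anxiety and sleep disturbance are named, as examples. Pain severity and pain intensity are not, and pain phenotype is a different construct.
- **Chance is not the only source of imbalance.** This stands for an analysis of completers, where differential drop-out could create a baseline difference. Such a difference would still not be mediation.
- **The SAP can settle it.** The point is not a missing detail. The article names unsuitable variables, and a SAP that follows it inherits them.

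**Conclusion.** The concern holds for values recorded before the first blinded dose. For baseline sleep and anxiety the expected indirect effect is zero, and likewise for pain unless baseline means the on-treatment week 1 average. Chance alone gives a standardised baseline difference with SE 0.092 SD (468) or 0.107 SD (351 evaluable). The planned analysis cannot answer the aim in the Background.

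This rests on two assumptions. First, baseline scores precede the first dose: the article labels Day 1 as baseline and ships the drug after randomisation, but does not state the order within Day 1. Second, blinding holds, so that knowledge of the assignment does not alter the baseline reports.

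The sentence should be fixed before analysis. It does not threaten the primary result.

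**What to change.** Align the mediation sentence in the Data analysis plan with the aim in the Background:
- Define the mediators as post-randomisation values or changes in the secondary outcomes, each model adjusted for the mediator's baseline value and sex at birth.
- Where daily ratings exist (pain intensity, pain interference, sleep quality), use values from before Day 28, so that the mediator precedes the PGIC. State which pre-dose value serves as their baseline, since the week 1 average is on treatment.
- Label week 4 PROMIS anxiety, sleep disturbance and pain interference as concurrent with the PGIC. Among the outcome measures described, anxiety has only a week 4 post-randomisation value.
- Keep baseline scores as covariates or moderators. If baseline pain is wanted there, name it. Say what pain severity means as distinct from pain intensity, or drop one term.
- Acknowledge that randomisation does not remove confounding between mediator and PGIC, so the results remain exploratory.

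**Cost:** a sentence or two of wording. The post-randomisation measurements are already planned, and neither the sample size nor the primary analysis changes. The downsides are the remaining confounding and the weaker time order of the week 4 mediators.

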#### Pain interference

Measured using the Pain Interference 4a short form items from the PROMIS-29 + 2 Profile v2.1 (PROPr) [34]. We will assess changes in pain interference comparing placebo against CBD over 4 weeks from baseline to the end of intervention.

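### The exploratory mediator list names pain level under two terms and omits pain interference and suicide ideation, so it does not match the stated aim (minor)

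*Protocol article*

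**What the plan says.** **Aim.** The Background commits the study to "investigate whether pain related symptoms (i.e., secondary outcomes) contribute to global improvement". It lists those outcomes as follows: "our secondary outcomes include pain severity, pain interference, sleep, suicide ideation, and mood". The Methods paragraph of the Abstract gives a similar list: "pain severity, pain interference, anxiety, suicide ideation, and sleep disturbance". Both put one pain-level outcome, called pain severity, next to a separate pain interference.

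**Definitions.** The section on secondary outcome measures defines five symptom outcomes: pain interference, pain intensity, anxiety, sleep disturbance and suicide ideation. For interference (PROMIS 4a) it says: "We will assess changes in pain interference comparing placebo against CBD over 4 weeks from baseline to the end of intervention". For intensity it says: "We will ask participants to report their “worst pain” level on a 0–10 numerical rating scale via a brief daily questionnaire", and then "we will compare the average of pain intensity for week 1 relative to the average of pain intensity for week 4". No measure called pain severity is defined there, and none appears among the daily items under Daily assessments.

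**Analysis.** The Data analysis plan contains one mediation statement: "We will explore baseline sleep, anxiety, pain severity, and pain intensity, as possible mediators of the treatment effect with the primary outcome".

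**The concern.** The aim equates the symptoms of interest with the secondary outcomes, but the mediator list is a different set. It uses two terms for what elsewhere looks like one pain-level outcome, and it leaves out pain interference, which is a defined secondary outcome, part of the eligibility screen and already collected. Suicide ideation is missing as well.

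At stake is what the exploratory analysis can conclude. If CBD improves PGIC partly by reducing how far pain limits daily life, a list without interference would miss part or all of that route. The undefined term also leaves open, until after the data are seen, which pain variable is meant.

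**Working it through.** **1. The plan's own figure.** The sample size is background only. For d = 0.30, 80% power and two-sided alpha 0.05 (two-sided is assumed), n per arm = 2 × (1.960 + 0.842)² / 0.30² ≈ 174.5, rounded up to 175. With 25% attrition, 175 / 0.75 = 233.3, rounded up to 234 per arm, or 468 in total. The stated 468 is reproduced, and nothing below changes it.

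**2. Outcomes against the mediator list.**

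| Secondary symptom outcome defined in the article | On the mediator list? |
|---|---|
| Pain interference (PROMIS 4a) | No |
| Pain intensity (daily worst pain, 0–10) | Yes, apparently under two names |
| Anxiety (PROMIS) | Yes |
| Sleep disturbance (PROMIS) | Yes |
| Suicide ideation (PANSI) | No |

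Four entries cover three of the five outcomes. The rest of the Data analysis plan covers covariate adjustment, effect modification, treatment effects on the secondary outcomes, change over time, relations with dose, and exploratory work whose stated example is moderation. None of it is stated to relate on-treatment interference to PGIC as a mediator.

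**3. What pain severity could mean.**
- The daily rating: one variable is then listed twice.
- The 3-month average rating in the screening questionnaire (Table 2): the article gives no on-treatment value for it, so it could not mediate.
- A slip for pain interference: the intended list then includes interference, but the printed text still needs correcting.

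The document does not settle which is meant. Each reading calls for an edit.

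**4. Size of the loss, on assumed inputs.** The protocol gives no inputs for this. Assume, in SD units, that CBD improves interference by 0.4, that interference has a slope of 0.5 on PGIC and carries the whole effect, and that interference and intensity correlate 0.6 within arm.

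- True indirect effect = 0.4 × 0.5 = 0.20 SD.
- Slope of PGIC on intensity when interference is left out = 0.5 × 0.6 = 0.30.
- Indirect effect recovered through intensity alone = (effect of CBD on intensity) × 0.30.

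| Effect of CBD on intensity (SD) | Recovered without interference (SD) | Share of 0.20 missed |
|---|---|---|
| 0 | 0 × 0.30 = 0.00 | 100% |
| 0.2 | 0.2 × 0.30 = 0.06 | 70% |
| 0.4 | 0.4 × 0.30 = 0.12 | 40% |

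With on-treatment interference in the model, its slope is 0.5 and that of intensity is 0, so 0.20 SD is recovered in all three rows.

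**5. The word baseline.** Step 4 needs mediators measured after treatment starts. Under randomisation the expected effect of treatment on a baseline score is 0, so the recovered indirect effect is 0 × 0.5 = 0.00 SD even for baseline interference. Adding interference to the list without changing the time point would therefore repair nothing.

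**The case against.** The strongest case on the other side has five parts.

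- **The time point is the larger fault in the sentence.** If the word baseline governs the whole list, the aim is unmet for every symptom, not only for interference. This stands, and the fix has to deal with it. It does not remove the present point: correcting only the time point would leave interference and suicide ideation off the list and pain level named twice.
- **Pain severity may be a slip for pain interference.** The Abstract and Background place those two terms side by side. This is possible and the document does not exclude it. On that reading the intended list is nearly right and the correction is a copy-edit.
- **The loss need not be total.** A reader might infer that an effect through interference would be reported as no mediation by pain at all. That holds only if CBD leaves intensity untouched, an extreme case given a correlation of 0.6. At intensity effects of 0.2 to 0.4 SD, 0.06 to 0.12 of 0.20 SD is still recovered.
- **Singularity and inflated standard errors are not established.** A reader might infer that one measure under two names makes the model impossible to fit, or that two near-copies inflate each slope's standard error by 1/√(1 − r²), which is 1.67 at r = 0.8 and 2.29 at r = 0.9. Both need the mediators to enter one model jointly. The plan does not say that they do, and with one mediator per model neither problem arises.
- **The list is exploratory and the article is condensed.** A fuller document may set out the mediators in detail, and the exploratory analyses also mention daily symptom assessments, which include interference. That lowers the weight of the point, but the article does print a specific list, and that list disagrees with its own aim and definitions.

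**Conclusion.** The point holds as a minor inconsistency confined to an exploratory analysis. The mediator list does not match the secondary outcomes that the Background says will be tested: pain level appears under two terms, one of them undefined, and pain interference and suicide ideation are absent. Read as printed, mediation through interference is not examined, and 40% to 100% of such an effect would be missed as CBD's assumed effect on intensity goes from 0.4 SD down to 0. That range rests on the assumed effect of 0.4 SD on interference, slope of 0.5 and correlation of 0.6, and on post-baseline mediators, which the printed sentence does not specify.

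The documents do not support saying that the trial cannot learn about interference. The treatment comparison on that outcome is planned and unaffected, as are the primary analysis, alpha and the sample size.

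**What to change.** In the Data analysis plan:

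1. Replace the two pain terms in the mediator sentence with pain intensity (the daily rating defined under Pain intensity) and pain interference (PROMIS 4a, defined under Pain interference).
2. Add suicide ideation (PANSI), or state why it is left out.
3. Replace baseline values with on-treatment values or change from baseline for all mediators.

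In the Abstract, the Background and the Data analysis plan, use the single term pain intensity for the daily rating.

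The cost is a few lines of protocol or SAP wording, best settled before unblinding so that the choice of pain measure is not made after the fact. No new data are needed: interference is measured from baseline to the end of intervention, anxiety, sleep disturbance and PANSI at baseline and week 4, and pain intensity daily.
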